## 2. Methods

### 2.1. Design and Participants

The design (Figure 1) is a two-branch random controlled design with participants who will receive the intervention protocol assigned to the intervention group and those who will receive the usual care assigned to the control group. The intervention will begin between 4–6 weeks after the initial evaluation. Usual care consists of attending pregnancy follow-up and monitoring appointments, resolving any questions that may arise during the process with the midwives, and attending group prenatal preparation classes. Participants will be assessed before and after, and one, three and six months after finishing the intervention. The trial is registered on ClinicalTrials.gov (accessed on 20 September 2024). The registration ID is NCT06609291.

### 2.2. Recruitment of Women

The midwives who collaborate in the research will invite pregnant women who attend obstetrics and gynecology consultations for pregnancy control and monitoring and who will give birth to their children in public hospitals in the Servizo Galego de Saúde (Spain) to participate in the study. Subsequently, the personnel in charge of the research will contact the women by telephone and again inform them verbally and in writing about the objective and methodology of the study. Once the consent form has been signed, the different questionnaires will be sent electronically. A questionnaire regarding sociodemographic variables (e.g., age, marital status, education level, employment status and personal monthly income), obstetric history and current pregnancy (e.g., number of previous pregnancies, planned pregnancy, complications) will be developed for this study.

After completion of the baseline questionnaire, participants will be randomly assigned to either the intervention or control group using block randomization, in a 2:1 ratio, using an online randomization program. Study personnel are unaware of which treatment group each participant will be assigned to at the time of the baseline assessment.

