## 1. Introduction

Anxiety is one of the most frequent disorders during the perinatal stage. Its prevalence is between 15% and 23% [1,2,3,4] during the pregnancy and between 3.7% and 15.0% [1,5] during postpartum. In Spain, the prevalence of anxiety ranges from 16.8 to 19.5% throughout pregnancy [3]. Additionally, one in ten women will experience comorbid anxiety and depression during pregnancy and one in twelve during the postpartum period [6]. The disparity in prevalence may be due to the moment of evaluation, the use of different evaluation instruments and cut-off points and cultural differences in relation to the importance given to mental health in a specific country and/or culture. Although its prevalence is high, research on treating anxiety during this period is recent [7,8].

Perinatal anxiety is associated with adverse health effects in women and their babies. Regarding mothers, it has been associated with an increased probability of developing postpartum depression [9], a higher risk of preeclampsia, obstetric complications and bonding problems [10,11,12]. As for newborns, they have been found to be more likely to have lower birth weight and poor cognitive development, among others [13,14], hence the importance of detecting and intervening early in prenatal anxiety to promote the well-being of mothers and children, because despite the negative consequences associated with perinatal anxiety, the majority of women are not identified or treated [7,15], as less than 15% receive treatment [16]. Given the high prevalence of prenatal anxiety and the potential for adverse consequences, early treatment is recommended [17,18]. Evidence on the effectiveness of psychological interventions during pregnancy is scarce [17,18,19,20], highlighting the importance of having specific interventions.

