### 2.3. Outcomes and Allocation of Participants to Trial Groups

#### 2.3.1. Primary Outcome

The primary outcome measure will be the difference in the mean anxiety scores between the intervention and control groups assessed by the EDS-3A, STAI and GAD-7 questionnaire before and at the end of the intervention, and one month, 3 months and 6 months after the intervention. Generalized anxiety disorder (GAD) will also be evaluated through the DSM-5 clinical interview at the same time points. In this case, the percentages found will be compared.

The Edinburgh Depression Scale-Anxiety Subscale (EDS-3A) is the anxiety subscale of the Edinburgh Postnatal Depression Scale (EPDS) [42]. Different studies, e.g., [43,44] have found that three items (3, 4, 5) can detect anxiety in women during the perinatal period. Each of the three items has four response options (0 = none, 1 = somewhat, 2 = quite a bit, and 3 = a lot). The total score of the subscale ranges from 0 to 9. The cut-off point used in the EDS-3A to detect anxious symptomatology will be ≥5 [45].

The State–Trait Anxiety Inventory (STAI) [46] assesses both the current level of anxiety and the individual’s predisposition to suffering from anxiety. It consists of 40 items, 20 of which refer to the state subscale (STAI-E), with the other 20 referring to the trait subscale (STAI-R). The score for each subscale ranges from 0 to 60, with higher scores indicating higher levels of anxiety. In this case, the State Anxiety Subscale (STAI-E) will be applied; the recommended cut-off point for women is greater than 31 (75th percentile).

Generalized Anxiety Disorder Screener (GAD-7) [47] is a self-administered instrument consisting of seven items with four response options. The total score ranges from 0 to 21, with the highest scores being the most severe. The GAD-7 has been validated for use in Spanish-speaking pregnant women [48]. The cut-off point used to detect anxiety symptoms will be ≥7 [49].

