### 2.4. Inclusion and Exclusion Criteria

Inclusion criteria include being pregnant with a gestational age ≤16, being over 18 years of age, understanding and speaking Spanish fluently, and giving consent to participate in the study. Additionally, participants must have access to the internet and a digital device (computer, tablet or smartphone). Those women who have a high-risk pregnancy or twins, are receiving pharmacological treatment for anxiety and/or depression or who do not give their consent will be excluded.

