### 2.7. Sample Size

Power calculations were conducted to determine the minimum sample size. As there was no research describing the efficacy of CBT delivered via videoconference in this population, power calculations were based on published RCTs of unguided CBT for antenatal depression [38]. To detect a between-group effect corresponding to Cohen’s d of 0.55, the minimum sample size for each group (α = 0.05, 80% power) was 53 participants. Therefore, we aimed to recruit a minimum sample of 140 participants to allow for expected attrition.

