### 2.8. Analysis Plan

The primary analysis will compare the mean scores of EDS-3A, STAI-E and GAD-7 between the two groups before and after the intervention and one month, 3 months and 6 months after the end of the intervention to evaluate the effectiveness of the protocol in preventing anxiety symptoms. Similar analyses will be performed for the secondary result on depressive symptomatology. For the GAD, the frequencies in the two groups will be compared at the same evaluation periods.

Regarding the effectiveness of treatment, descriptive statistics will be calculated for all questionnaires. Variance analyses for repeated measurements will be performed to compare the differences between each initial score obtained with the different administered questionnaires and the scores at T1 (end of treatment), T2 (after 1 month), T3 (after 3 months) and T4 (after 6 months) will be evaluated. Bonferroni post hoc comparisons will also be conducted. The number of evaluations compared will need to be taken into account to adjust the *p*-value in the Bonferroni test with the aim of minimizing type 1 errors. The treatment effect will be calculated using Cohen’s d for each of the follow-up times. The Reliable Change Index will be calculated for each time in order to determine any significant clinical changes occurring in each individual case post-treatment. To compare differences in GAD, the chi-square test and Fisher’s exact test will be used in the contrast of 2 × 2 tables. In addition, Cochran’s Q test will be used to determine the existence of differences across time points and McNemar’s test will be used to compare the differences in categorical variables between time points in a paired manner.

Data will be analyzed using the Statistical Package for Social Science (SPSS) for Windows version 23.0.

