## 3. Intervention

### 3.1. Rationale

The intervention was based on the principles of cognitive–behavioral therapy (CBT) and transdiagnostic treatments for emotional problems and includes three sections that address the main components of CBT: thoughts, pleasant activities and social contacts. CBT is one of the interventions that has obtained the best results for the treatment and prevention of perinatal anxiety [7,52,53]. On the other hand, transdiagnostic interventions may be more beneficial than specific interventions for each disorder, as scientific evidence suggests [7,37]. The need to develop this perinatal anxiety prevention program aimed at pregnant women is justified by the high prevalence of anxiety in the perinatal stage, as well as its possible consequences for both the mother and the baby [8,54]. Furthermore, there is a high comorbidity between symptoms of perinatal depression and anxiety [6], which indicates the importance of having a transdiagnostic intervention. Another aspect that highlights the need for a program of this type is the scarcity of existing psychological interventions to treat anxiety during pregnancy and postpartum [8,55]. A prevention program has been chosen because it would allow anxiety to be treated before it becomes a problem for the mother and her baby and would prevent future suffering [26]. Specifically, it would be a universal prevention program intended for all pregnant women regardless of whether or not they are at risk of anxiety. These programs have the advantage of increasing awareness about perinatal mental health as they provide information about its prevalence and risk factors, as well as tools to cope with emotional distress and increase the support network.

A CBT prevention program has been selected for development because it is found to obtain some of the best results in clinical practice [7,24]. The techniques included in the program, such as cognitive restructuring, behavioral activation or social support, have been selected because they repeatedly appear in the reviewed interventions that have shown greater effectiveness [7,8,24,32]. It should be noted that the intervention will not exclusively address anxiety, but also depression, due to the high comorbidity they present [6].

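### Baseline anxiety is known before allocation but is neither named as a stratification factor nor used in the between-group GAD tables and effect sizes: a modest loss of precision and credibility

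*Protocol article*

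**What the plan says.** All references are to the protocol article.

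- **Allocation (2.2).** The method is stated as "participants will be randomly assigned to either the intervention or control group using block randomization, in a 2:1 ratio", by an online program. On timing: "After completion of the baseline questionnaire, participants will be randomly assigned". No stratification factor or block size is given.
- **Who enters (3.1, 2.4).** On the programme: "it would be a universal prevention program intended for all pregnant women regardless of whether or not they are at risk of anxiety". No symptom limit is set. The only exclusion bearing on current anxiety is for women who "are receiving pharmacological treatment for anxiety and/or depression".
- **How many are anxious (1).** "In Spain, the prevalence of anxiety ranges from 16.8 to 19.5% throughout pregnancy".
- **A ready-made stratum (2.3.1).** "The cut-off point used in the EDS-3A to detect anxious symptomatology will be" 5 or more. STAI-E and GAD-7 have cut-offs of their own.
- **Size of effect (2.7).** "To detect a between-group effect corresponding to Cohen’s d of 0.55", 53 women per group are needed, and 140 are to be recruited. No effect on a frequency is quantified.
- **Analysis (2.8).** Scores go into repeated-measures analysis of variance that sets the initial score against T1-T4. Cohen's d is reported at each follow-up. For GAD, "the frequencies in the two groups will be compared at the same evaluation periods", by chi-square or Fisher's exact test on 2 × 2 tables. No baseline term is stated for the last two.

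**The concern.** Blocking fixes the number of women per arm, not the number of anxious women per arm. At 2:1, 140 women give about 93 and 47, so only about 8-9 of the already-anxious women are expected in the control arm. A small count of that kind can move noticeably by chance.

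Baseline anxiety is likely to be among the strongest predictors of later anxiety scores and of GAD. A trial that claims prevention will be judged partly on whether its arms started alike. A visible difference at entry invites doubt about any later difference that has not been adjusted for it. The information that would remove the doubt is collected anyway, before allocation.

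**Working it through.** **1. The plan's own figure.** n per group = 2(1.960 + 0.842)²/0.55² = 51.9. The t-based solution is 52.87, rounded up to 53. The stated figure is reproduced (two-sided, equal groups).

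**2. Anxious women at entry.** 0.168 × 140 = 23.5 and 0.195 × 140 = 27.3, so about 24-27. Assumption: the cited prevalence holds in this sample and on the instrument used.

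**3. Chance imbalance.** Let p be the anxious share, with arms of 93 and 47.
- SD of the difference in anxious share = √[p(1−p)(1/93 + 1/47)].
- p = 0.168: √(0.1398 × 0.0320) = 6.7 points. p = 0.195: √(0.1570 × 0.0320) = 7.1 points.
- The exact hypergeometric split of 25 anxious women gives SD 6.9 points, and 1.96 × 6.9 = 13.5 points.
- The 95% range of the count in the intervention arm is 12 to 21. That is 12/93 = 13% against 13/47 = 28%, or 21/93 = 23% against 4/47 = 9%.

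**4. What this does to mean scores.** Assume a normal score cut at 25/140. Anxious and non-anxious women then differ by about 1.78 SD.
- 95% shift at baseline: 0.135 × 1.78 = 0.24 SD.
- 95% shift at follow-up: 0.24 × 0.5 = 0.12 SD, or 0.24 × 0.7 = 0.17 SD, for assumed baseline-to-follow-up correlations r of 0.5 and 0.7.
- A shift of 0.55 SD would need a gap of 0.55/1.78 = 31 points. The probability is about 2 in a million at baseline and below 1e-10 at follow-up.
- Simulated type I error without stratification (8,000 trials per setting, assumed blocks of 6) is 4.6-5.2%.

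**5. What stratified blocks gain.**
- With 24-27 anxious women and blocks of 3 or 6, the largest gap falls to 0.2-3.4 points. For example, with 24 women, 16/93 − 8/47 = 0.2 points.
- Anxiety status explains 1.78² × 0.1467 = 46% of the baseline variance, hence 0.46r² of the follow-up variance. The SD of the unadjusted mean difference falls by 1 − √(1 − 0.116) = 6% (r = 0.5) to 1 − √(1 − 0.228) = 12% (r = 0.7).
- Power at d = 0.55, without and with stratified blocks: unadjusted follow-up score 86.8% and 86.8% (r = 0.5), 86.3% and 89.0% (r = 0.7). Change score 86.6% and 87.4%, then 97.4% and 98.0%.

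**6. What baseline adjustment gains.** With the continuous baseline as a covariate, the simulated SD of the mean difference falls from 0.179 to 0.156 (r = 0.5) and from 0.179 to 0.129 (r = 0.7), and stratifying the blocks changes it by at most 0.002. For mean scores, adjustment does most of the work.

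**7. A frequency outcome.** A test stratified by baseline status gains about 1-5 points of power over the crude test. I repeated this for one setting: 18% anxious, the same cut-off at follow-up, d = 0.55 on the underlying score, blocks of 6. Power went from 50.7% to 52.5% (r = 0.5) and from 50.5% to 56.9% (r = 0.7) without stratified blocks, and adding them changed the stratified test by less than 1 point. The gain is a few points and comes mainly from the test. The documents give no GAD rate, so it cannot be computed for GAD itself.

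**The case against.** **The chance imbalance is harmless to the tests.** It is already in the standard error, and type I error stays near 5%. This stands: the issue is precision and credibility, not bias.

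**The analysis already uses baseline.** The repeated-measures analysis sets the initial score against T1-T4. This also stands, so it would be wrong to infer that section 2.8 ignores baseline throughout. The gap is confined to the GAD tables and the per-visit Cohen's d.

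**The article may be condensed.** It does not say that the blocks are unstratified, and a full protocol may name a factor. This stands for section 2.2, and the fix is conditional on it. It does not reach section 2.8, which states a crude chi-square or Fisher test.

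**The stratum is only a proxy.** The cited prevalence is not specific to EDS-3A of 5 or more, and the introduction itself says that prevalence varies with instrument and cut-off. The drug-treatment exclusion may lower the share. GAD is diagnosed by SCID, so EDS-3A status protects those tables imperfectly. All of this stands and limits how firmly any gain can be stated.

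**A tempting stronger reading** is that an uneven split could mimic or hide the expected effect. A 9-point baseline gap, equal to halving an 18% frequency, arises in roughly one trial in five. But no such halving is in the protocol, and this sets a baseline gap against a follow-up effect. In the normal model a 9-point gap shrinks to about 2.6 points at follow-up (r = 0.5) or 4.0 points (r = 0.7). A 9-point follow-up gap caused by the split alone has a probability of 0.2-0.4% at r = 0.7, and far less at r = 0.5.

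**Conclusion.** The point holds as a low-cost improvement, not as an error that threatens the trial. As described, allocation leaves the balance of baseline anxiety to chance, and two planned between-group summaries make no stated use of it. The documents do not support a claim of bias or of a spurious d = 0.55: the likely follow-up shift of 0.12-0.17 SD is under a third of that effect.

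What is lost is some precision, plus the credibility of the GAD comparison should a split such as 13% against 28% appear. The figures assume 93:47 allocation, the cited prevalence, a normal underlying score and correlations of 0.5-0.7. None of these is established for this sample.

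**What to change.** **Section 2.8 (worth doing at any stage before the data are analysed).** State that between-group score comparisons and Cohen's d at each visit are adjusted for the continuous baseline score. Replace the crude chi-square or Fisher comparison of GAD between groups by a Cochran-Mantel-Haenszel test stratified by baseline anxiety status.

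**Section 2.2 (only if recruitment has not started and the full protocol does not already do so).** Stratify the online blocks by baseline anxiety status, for example EDS-3A below 5 against 5 or more, keeping 2:1 in each stratum. If recruitment has begun, leave allocation alone: a mid-course switch gives a mixed scheme to which the gains above do not apply. If blocks are stratified, the analysis must carry the stratum. In the simulations an unadjusted test of follow-up scores after stratified blocks had type I error of only 2.7-3.9%, which wastes part of the gain.

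**Cost.** One or two sentences in each section and one program setting. The baseline scale must be scored before allocation is released, and recruitment may end with one extra incomplete block. No additional women or visits are needed.

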### 2.3. Outcomes and Allocation of Participants to Trial Groups

#### 2.3.1. Primary Outcome

The primary outcome measure will be the difference in the mean anxiety scores between the intervention and control groups assessed by the EDS-3A, STAI and GAD-7 questionnaire before and at the end of the intervention, and one month, 3 months and 6 months after the intervention. Generalized anxiety disorder (GAD) will also be evaluated through the DSM-5 clinical interview at the same time points. In this case, the percentages found will be compared.

The Edinburgh Depression Scale-Anxiety Subscale (EDS-3A) is the anxiety subscale of the Edinburgh Postnatal Depression Scale (EPDS) [42]. Different studies, e.g., [43,44] have found that three items (3, 4, 5) can detect anxiety in women during the perinatal period. Each of the three items has four response options (0 = none, 1 = somewhat, 2 = quite a bit, and 3 = a lot). The total score of the subscale ranges from 0 to 9. The cut-off point used in the EDS-3A to detect anxious symptomatology will be ≥5 [45].

The State–Trait Anxiety Inventory (STAI) [46] assesses both the current level of anxiety and the individual’s predisposition to suffering from anxiety. It consists of 40 items, 20 of which refer to the state subscale (STAI-E), with the other 20 referring to the trait subscale (STAI-R). The score for each subscale ranges from 0 to 60, with higher scores indicating higher levels of anxiety. In this case, the State Anxiety Subscale (STAI-E) will be applied; the recommended cut-off point for women is greater than 31 (75th percentile).

Generalized Anxiety Disorder Screener (GAD-7) [47] is a self-administered instrument consisting of seven items with four response options. The total score ranges from 0 to 21, with the highest scores being the most severe. The GAD-7 has been validated for use in Spanish-speaking pregnant women [48]. The cut-off point used to detect anxiety symptoms will be ≥7 [49].

The SCID [50] is a semi-structured interview that determines formal diagnosis according to the Diagnostic and Statistical Manual of Mental Disorders (DSM-5). To diagnose generalized anxiety, you need to have had anxiety on most days in the last 6 months in at least three contexts of your daily life and show three of the six anxiety symptoms that are described in the manual. The use of such interviews improves diagnostic reliability by standardizing the assessment process and increases diagnostic validity by facilitating the application of DSM diagnostic criteria and the systematic enquiry for symptoms that might otherwise go unnoticed.

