## Abstract

**Background:** Anxiety is one of the most frequent disorders during the perinatal stage that is associated with adverse health effects in women and their babies. In spite of this, preventive interventions during this stage are scarce. A long-distance intervention carried out during pregnancy can be an effective and accessible resource to help improve women’s emotional state. The objective of this study is to present and assess the effectiveness of a telepsychology cognitive–behavioral preventive intervention during pregnancy to manage anxiety. **Methods:** A random clinical trial will be carried out among pregnant women in Spain. The psychological intervention will take place via videoconference in seven weekly sessions, lasting one hour each, with groups of 6–8 pregnant women. Study outcomes will be collected via online questionnaires at five points in time: pre-intervention (baseline: t0), post-intervention (baseline: t1), follow-up at 1 month (t2), follow-up at 3 months (t3) and follow-up at 6 months (t4). The control group will receive usual pregnancy care (attendance at pregnancy follow-up consultations and information and answers to frequently asked questions provided by the midwife). Our primary hypothesis is that the intervention will decrease the frequency of women who present anxious symptomatology during pregnancy. The second objective is to analyze the effectiveness of this intervention to prevent depressive symptomatology during pregnancy, as well as postpartum anxiety and depressive symptomatology. The primary outcome measure is the difference in the mean anxiety score between the intervention and control groups assessed by the Edinburgh Depression Scale-Anxiety Subscale (EDS-3A), the State–Trait Anxiety Inventory (STAI) and Generalized Anxiety Disorder Screener (GAD-7) at the end of the intervention and at 1, 3 and 6 months postpartum. Generalized anxiety disorder (GAD) will be evaluated with the SCID clinical interview at the same time points. The secondary outcome will be determined by using the EPDS at the same time points. **Conclusions:** The results will determine whether a cognitive behavioral therapy applied via videoconference is well accepted by pregnant women, and if it is effective in preventing anxiety and emotional symptoms during the perinatal stage. If this intervention is an effective and useful resource among pregnant women, it can be implemented as a tool in Spanish healthcare.

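### The primary outcome and primary analysis count the pre-randomisation score as a between-group comparison, contrary to the abstract; whether this costs power depends on a test the plan does not name

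*Protocol article*

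**What the plan says.** - **Primary outcome (2.3.1).** The difference between arms in mean EDS-3A, STAI and GAD-7 scores "before and at the end of the intervention, and one month, 3 months and 6 months after the intervention". That makes five times, the first before treatment.
- **Primary analysis (2.8, first paragraph).** Mean scores are compared "between the two groups before and after the intervention and one month, 3 months and 6 months after the end of the intervention". GAD frequencies are compared between arms at the same assessments, with chi-square and Fisher tests on 2 × 2 tables.
- **Secondary outcome (2.3.2).** The EPDS comparison takes over the same times.
- **Order of events (2.2).** "After completion of the baseline questionnaire, participants will be randomly assigned".
- **Abstract.** The primary outcome is assessed "at the end of the intervention and at 1, 3 and 6 months postpartum", with no baseline.
- **Model (2.8, second paragraph).** "Variance analyses for repeated measurements will be performed to compare the differences between each initial score obtained with the different administered questionnaires and the scores". The later scores meant are those of T1 to T4. Further on: "The treatment effect will be calculated using Cohen’s d for each of the follow-up times".
- **Multiplicity (2.8).** "The number of evaluations compared will need to be taken into account to adjust the" p-value in the Bonferroni test. No number is given.

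**The concern.** A score recorded before allocation has an expected difference of zero between randomised arms. As one of the comparisons that make up the primary outcome, it adds no information on the intervention and invites a chance imbalance to be reported as a primary result. For GAD this is direct: a 2 × 2 test between arms at t0 tests only whether randomisation produced an imbalance.

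Two further costs are possible, depending on how section 2.8 is carried out. A group effect averaged over all five visits would include one visit with no effect. A Bonferroni divisor that counts the t0 comparison would make each real follow-up comparison stricter.

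**Working it through.** **Inputs.** From section 2.7: d = 0.55, α = 0.05, power 80%, 53 per group, 140 recruited. From section 2.2: 2:1 allocation. Assumptions not in the article: d = 0.55 constant over T1–T4, zero at t0, unit variance, equal correlation r between visits (range 0.3 to 0.8). Two completer splits are shown: 53/53 as planned, and 71/35, which is the same 106 women at 2:1.

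**1. The plan's own figure.** A two-sided two-sample t-test with d = 0.55, α = 0.05 and 80% power needs 52.87 per group, so 53. The figure reproduces (a one-sided test would give 41). It rests on one comparison at an unadjusted 0.05.

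**2. If the test is the five-level group main effect.**
- Mean effect with t0: (0 + 4 × 0.55)/5 = 0.44. Without t0: 0.55.
- Variance of a woman's mean over k visits: (1 + (k − 1)r)/k. At r = 0.5 this is 0.600 for k = 5 and 0.625 for k = 4.
- Standardised effects at r = 0.5: 0.44/√0.600 = 0.568 and 0.55/√0.625 = 0.696.

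Power, two-sided 0.05, noncentral t:

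| r | 53/53 with t0 | 53/53 without | 71/35 with t0 | 71/35 without |
|---|---|---|---|---|
| 0.3 | 92.3% | 98.3% | 88.9% | 96.9% |
| 0.5 | 82.6% | 94.4% | 77.8% | 91.6% |
| 0.7 | 73.0% | 89.0% | 67.8% | 85.0% |
| 0.8 | 68.7% | 86.0% | 63.4% | 81.6% |

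**3. If each visit is a separate between-group test and t0 is counted.** The level is 0.05/5 = 0.010 instead of 0.05/4 = 0.0125. Single-visit power is 58.3% instead of 61.5% at 53/53, and 51.8% instead of 55.0% at 71/35. The loss is about 3 points.

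**4. If t0 is the reference.** The effect on mean change is 0.55 − 0 = 0.55, undiluted. Its variance is (1 + 3r)/4 + 1 − 2r. At 53/53, power is 85.1%, 94.4% and over 99% for r = 0.3, 0.5 and 0.8. The five-level group-by-time test has 66.7%, 82.7% and 99.8%. At r = 0.3 both are below the 92.3% in the table, but that comes from the noise of a weakly correlated baseline and, for the interaction, its four degrees of freedom; the effect itself is not diluted. Four contrasts of T1–T4 against t0 give a divisor of 4, so t0 uses no alpha.

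**The case against.** The second paragraph of 2.8 sets the initial score against T1–T4 and gives effect sizes only for follow-up. Read that way, the plan already uses t0 as it should, and the wording in 2.3.1 merely echoes the assessment schedule in 2.1. A journal article may also leave the choice of ANOVA term and the Bonferroni divisor to a fuller document. Even on the unfavourable reading, 53 per group at r = 0.5 still gives 82.6%, above the planned 80%; the 71/35 figures also carry the cost of 2:1 allocation, which is a separate matter. Finally, simply deleting baseline could damage planned within-person analyses.

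Much of this stands. A reader might infer that the primary test is diluted, or that t0 takes a share of the Bonferroni allowance. The article supports neither as fact: it names no five-visit main effect as the primary test and fixes no divisor. The point about within-person analyses also stands and shapes the fix.

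What does not stand is that nothing needs correcting. The sentence in 2.8 that is labelled primary is a between-group comparison with t0 included, and it disagrees with the abstract. That is a contradiction in stated text, not omitted detail. The reference-value reading also does not cover the between-arm GAD tests, where t0 has no such role. If baseline was meant as reference, the definition in 2.3.1 is wrong as written.

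**Conclusion.** The point holds as an error of definition: a pre-randomisation score is listed among the between-group comparisons of the primary outcome and primary analysis, is carried over to the EPDS and GAD, and conflicts with the abstract and with the times given for Cohen's d.

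Its cost is conditional. Under a five-visit group main effect the average effect falls by 20% (0.55 to 0.44 SD). At r = 0.5 the loss is about 12 power points at 53/53 and 14 at 71/35; at 53/53 it ranges from about 6 to 17 points over r = 0.3 to 0.8. Under a Bonferroni count that includes t0 it is about 3 points. Under change from baseline or group-by-time there is no dilution and no alpha cost. The power figures rest on the assumed constant effect and correlations. The article does not show which case applies, so no loss of power should be stated as established.

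**What to change.** - In 2.3.1, 2.3.2 and 2.8, restrict the between-group outcome comparisons, including the GAD chi-square and Fisher tests, to the post-randomisation visits, as the abstract does.
- State that t0 serves as the baseline value (covariate or reference) and is described by arm.
- Count only post-randomisation between-group comparisons in the Bonferroni divisor.
- Keep t0 in the planned within-person analyses: Reliable Change Index, Cochran's Q and McNemar.

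Alignment with the abstract here means leaving out baseline. The abstract dates the follow-ups from birth and the body dates them from the end of the intervention; that difference has to be settled separately.

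The cost is wording only. No new data are needed and no planned analysis is lost, provided the last bullet is kept.
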